The incidence of each PICS-F impairments (psychological, physical, and cognitive) at T3 and T4, will be determined by classifying subjects according to the proposed cut-off scores. The number of subjects showing a given PICS-F impairment will be divided by the total number of subjects at the specific point of the study. Then, to analyze factors associated with PICS-F impairments, bivariate and multivariate analyses will be conducted. Cross-sectionally, Chi-square or Fisher's exact test will be applied in case of analyzing two or more categorical variables. In the case of two continuous numerical variables, Pearson or Spearman correlation test will be used. If one dependent variable is continuous normally distributed and the independent variable is categorical, then a t-test (two groups) or ANOVA test (three or more groups) will be applied; if the dependent variable is non-normally distributed, Mann-Whitney U test (two groups) or Kruskal-Wallis test (three or more groups) will be applied. Bivariate analyses, along with factors identified in the literature, will help to identify potential independent variables for multivariate models.

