a Models will be tested with T3 and T4 dependent variables separately. SOFA: sequential organ failure assessment score; ICU: intensive care unit; BI: Barthel index; MHA: mental health antecedents; LOS = length of stay; PHQ-4: patient health questionnaire; IES-6: impact of event scale; mMOS-SSS: modified medical outcomes study social support scale; BRCS: brief resilience coping scale; SF-36 VT: short-form health survey, vitality subscale; MEFO: memory, fluency, and orientation test.

**Sample Size:** The study sample size will consider the following values: alpha = 5%, a beta = 80%, and precision of estimate = 5%. Because of the lack of studies utilizing the same questionnaires to establish PICS-F incidence, a 20% incidence of PTSD symptoms reported in a study utilizing an IES-6  $\geq 1.75$  will be utilized. Based on these parameters, the calculation of the sample size is obtained by the following formula:  $[Z^2 \times P \times (1-P)]/e^2$  where  $Z$  is the value from standard normal distribution associated with a particular confidence interval (CI), which in this case is set at 95%,  $P$  is the expected true proportion in the population, and  $e$  is the desire precision level. Consequently, the initial sample size is 247 RFM.

This sample size will be adjusted for a finite population. In this study, the finite population will be 600 since it represents the average 2019-2020 number of ICU admissions ( $\pm 550$ ) plus a 10% of projected increase during 2023. Data of 2021 will not be considered since it was heavily influenced by the COVID-19 pandemic waves of ICU admissions and it is not likely to be representative of 2023. Then, the adjusted sample size is obtained using the following formula:  $(\text{finite population} \times \text{initial sample size}) / (\text{finite population} + \text{initial sample size})$ . Thus, the adjusted sample size will be 175 RFM. However, considering the attrition rates reported in the literature, 40% of losses are contemplated leaving 292 RFM as the final adjusted sample size.

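### Incidence at 3 and 6 months is a proportion of those assessed, with 40% loss planned for only by enrolling more relatives, so outcome-related loss would bias it by a few points

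*Protocol*

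**What the plan says.** For the first objective, the Statistical analyses section of the protocol classifies relatives by the cut-offs at T3 and T4. The count with each impairment "will be divided by the total number of subjects at the specific point of the study". The natural reading is those assessed at that visit.

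The Sample Size paragraph sets "alpha = 5%, a beta = 80%, and precision of estimate = 5" per cent and takes as its expected proportion "a 20% incidence of PTSD symptoms reported in a study utilizing an IES-6" at or above 1.75. It then states "Consequently, the initial sample size is 247 RFM", corrects for a finite population, and concludes that "the adjusted sample size will be 175 RFM". Attrition enters once: "40% of losses are contemplated", which brings the target to 292.

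Relatives are withdrawn if the patient dies, and only their data up to that date are used (Exclusion criteria; Data collection & enrollment process). PHQ-4 and SF-36 VT are collected at all four visits and IES-6 from T2. Table 1 lists MEFO at T1 and T2, together with education, income and kinship. The incidence formula uses none of these.

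**The concern.** Dividing by those assessed is unbiased for the enrolled families only if loss is unrelated to the impairment. Enrolling 292 to keep 175 secures the width of the interval but does nothing about who the 175 are.

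A link between loss and outcome is plausible. The questionnaires are estimated to take 50-55 minutes, T3 and T4 are done by phone, and a distressed or exhausted relative may be harder to retain. The reverse is also possible, since relatives who are coping well may see no reason to continue. In either case the reported incidence would be off by an amount that its confidence interval does not show.

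**Working it through.** **Inputs from the protocol.** P = 20%; precision e = 5 points; confidence level "which in this case is set at 95" per cent, so Z = 1.96; "the finite population will be 600"; loss L = 40%. Clinically significant fatigue of 43-53% comes from the Background section on physical and cognitive impairments. The relation between loss and outcome is not given, so it is varied.

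**The protocol's own chain.**
- Initial size: 1.96² × 0.2 × 0.8 / 0.05² = 245.9, so 246 (stated 247, an immaterial difference).
- Finite population: 600 × 247 / (600 + 247) = 174.97, so 175.
- Loss: 175 / 0.6 = 291.7, so 292.
- 95% half-width at n = 175: 1.96 × √(0.16/175) = 5.9 points, or 5.9 × √(425/599) = 5.0 points with the finite-population correction.

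The chain reproduces. Loss enters only through the last division by 0.6.

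**Bias.** Let d1 and d0 be the loss in cases and non-cases, with P·d1 + (1 − P)·d0 = L. The expected observed proportion is P(1 − d1)/(1 − L). Equivalently, bias = L × (incidence in retained − incidence in lost). At L = 40%, a 5-point bias needs an incidence gap of 5/0.40 = 12.5 points.

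P = 20%, L = 40%:

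| Odds ratio of loss | Loss, cases / non-cases | Observed | Shift (points) |
|---|---|---|---|
| 1.25 | 44.3% / 38.9% | 18.6% | −1.4 |
| 1.5 | 47.9% / 38.0% | 17.4% | −2.6 |
| 1.75 | 51.0% / 37.3% | 16.3% | −3.7 |
| 2 | 53.6% / 36.6% | 15.5% | −4.5 |
| 2.15 | 55.0% / 36.2% | 15.0% | −5.0 |
| 2.5 | 57.9% / 35.5% | 14.0% | −6.0 |

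Check of the 1.75 row: 0.2 × 0.5096 + 0.8 × 0.3726 = 0.400, and 0.2 × 0.4904 / 0.6 = 0.1635. In the opposite direction, 25% loss in cases against 43.75% in non-cases gives 25.0%, a shift of +5.0.

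**Effect on the interval** (odds ratio 1.75). SE = √(0.1635 × 0.8365/175) = 0.0280 and bias/SE = 0.0365/0.0280 = 1.31. Coverage = Φ(1.96 − 1.31) − Φ(−1.96 − 1.31), about 74% instead of 95%.

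**Commoner impairment** (L = 40%, odds ratio 1.75).
- P = 43%: 0.43 × (1 − 0.4766)/0.6 = 37.5%, a shift of −5.5.
- P = 53%: 0.53 × (1 − 0.4625)/0.6 = 47.5%, a shift of −5.5.
- The 5-point threshold falls to an odds ratio of about 1.66.

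**Smaller relevant loss** (assumption: 20% among survivors' families, odds ratio 1.75).
- P = 20%: 0.2 × (1 − 0.2782)/0.8 = 18.0%, a shift of about −2.0.
- P = 43%: 0.43 × (1 − 0.2515)/0.8 = 40.2%, a shift of −2.8.
- A 5-point bias would now need an incidence gap of 5/0.20 = 25 points.

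**Extreme bounds.** If 20% is observed and 40% are lost, the full-cohort value lies between 0.6 × 20% = 12% and 12% + 40% = 52%.

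**The case against.** The strongest case on the other side has four parts.

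- **Size.** A reader might infer that modest outcome-related dropout moves the estimate by more than the stated 5 points. At the protocol's P = 20% it does not: odds ratios up to 1.75 stay below 4 points, and passing 5 needs a loss gap above 18.75 percentage points. This part stands.
- **Which loss counts.** The target is families of ICU survivors, so withdrawal because the patient died is not selection bias for that target. The 40% is not split by cause or by visit, and the denominator is visit-specific, so a relative seen at T3 and lost later still counts at T3. This stands and reduces the likely bias, by an amount the protocol does not allow one to fix.
- **Predictors of loss.** A reader might also infer that T1 and T2 scores are known to predict loss. Table 1 treats them as candidate predictors of the outcome, and nothing in the protocol shows that they predict loss. Adjustment may therefore remove only part of the bias.
- **SAP territory.** A crude proportion is ordinary in an exploratory study, and missing-data handling is commonly left to an analysis plan, which is not shown here. The absence of a missing-data policy is therefore not a fault in itself. But the protocol does write down an estimator for its first objective, and an analysis plan would have to add to that formula or override it. The point rests on the formula.

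**Conclusion.** The point holds in a limited form. The written estimator carries no protection against outcome-related loss, and the increase to 292 does not supply any. Under the protocol's P = 20% and a full 40% loss, the plausible bias is about 1.4 to 3.7 points for loss odds ratios of 1.25 to 1.75, and it reaches 5 points only at about 2.15. For fatigue at 43-53%, an odds ratio of 1.75 is enough to pass 5 points. If loss among survivors' families is nearer 20%, the P = 20% shift at 1.75 is about 2 points.

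All of this depends on an assumed link between loss and outcome, whose size and direction the protocol does not give. The documents do not support saying that the incidence will be wrong by more than its precision. They do support saying that it could be wrong by a material part of it, and that the data needed to reduce the problem are already planned.

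**What to change.** Keep the visit-specific observed proportion as a reported figure, and add to the incidence paragraph of the Statistical analyses section:

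1. An estimate of T3 and T4 incidence among enrolled relatives whose patient is alive at the visit, by multiple imputation or inverse-probability weighting. Use T1 and T2 PHQ-4, SF-36 VT and MEFO, T2 IES-6 where available, and the sociodemographic variables.
2. A comparison of T1 scores, and T2 scores where available, between retained and lost relatives, with losses because the patient died counted separately at each visit.
3. A bounding analysis for loss not at random, giving the incidence in the lost that would change the conclusion.

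The cost is analysis work only, since no new data collection is needed. The downsides are a slightly wider interval and reliance on missing-at-random given the T1 and T2 data. Relatives lost before T2 have no IES-6, so T1 data alone must serve for them.

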### **Specific Aims**

1. To describe the sociodemographic and clinical features of both family members and ICU patients.
2. To determine the level of anxiety symptoms, depressive symptoms, PTSD symptoms, cognitive impairment, fatigue, perceived social support, resilience, family satisfaction, and caregiver burden among family members of ICU survivors of a public hospital in Chile.
3. To explore the association between contextual factors, primary stressors, secondary stressors, psychosocial resources, and PICS-F impairments among family members of ICU survivors of a public hospital in Chile.
4. To evaluate the extent to which secondary stressors (family satisfaction or caregiver burden) significantly contribute to PICS-F impairments among family members of ICU survivors of a public hospital in Santiago, Chile.

**Hypotheses:** The proposed hypotheses for the study are:

1. Family members of ICU survivors will experience at least one PICS-F impairment at three and/or six months after hospital discharge.
2. Primary stressors (anxiety, depressive, PTSD symptoms, fatigue, or cognitive impairment) and/or psychosocial resources (social support or resilience) will be associated with at least one PICS - F impairment at three and/or six months after hospital discharge.
3. After controlling for contextual factors, primary stressors, and psychosocial resources, at least one secondary stressor (family satisfaction or caregiver burden) will significantly contribute to the development of at least one PICS - F impairment at three and/or six months after hospital discharge.

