## Subjects

**Inclusion criteria:** All adult family members (≥ 18 years old) identified as the patient's representative, Spanish speakers, and likely to become responsible for providing or coordinating care after hospital discharge will be eligible. Besides, the family member's ICU patient must have at least 48 hours in the ICU, be > 18 years old, and receive respiratory support (noninvasive ventilation, high-flow nasal cannula, or invasive mechanical ventilation).

**Exclusion criteria:** Family members of ICU patients with a high impending death risk or likely to be discharged from the ICU in the following 24 hours after screening will be excluded. Family members will be withdrawn at any point of the study if the patient dies.

**Variables:** To explore PICS-F impairments incidence and the potential associations with other variables, the following independent variables measured through questionnaires will be used:

- **Anxiety and Depressive Symptoms:** The Patient Health Questionnaire for Depression and Anxiety (PHQ-4) is an ultra-brief screening tool utilized to explore the occurrence of anxiety and depressive symptoms according to the DSM – IV criteria. PHQ-4 comprises 4 items for cardinal symptoms of both anxiety (2 items) and depressive (2 items) disorders. Answers are scored utilizing a Likert scale ranging from 0 ("Not at all") to 3 ("Nearly every day"). A cut-off value of 6 points for the sum of all items (PHQ-4 ≥ 6) has been utilized to identify subjects with a potential anxiety/depressive disorder. The Chilean-Spanish

version of the PHQ-4 has shown an adequate internal consistency. PHQ-4 will be used in all 4 time points of the study.

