- **Caregiver Burden:** The Zarit Burden Interview (ZBI) was developed to subjectively measure the burden of caring for an adult with a disabling condition. ZBI is composed of 22-items with a Likert scale extending from 1 ("never") to 5 ("nearly always") with higher scores reflecting a higher level of burden. The Chilean Spanish version of the ZBI has reported an adequate internal consistency. In this study, the 7-item version of the ZBI will be employed which includes items 2, 3, 6, 9, 10, 17, and 22 of the original questionnaire. A cut-off value of  $\geq 17$  points for the sum of all 7 items has been established to classify subjects with intense caregiver burden. Caregiver burden will be measured only in T3 and T4.

All questionnaires in this study are self-reported and the average time for completing them, including the MEFO test, is estimated in 50-55 minutes. Besides, relevant family members' sociodemographic variables plus demographic and clinical data from the patient will be collected at each time point. Detailed information on these variables is presented in the statistical analyses section (Table 1).

**Outcome:** To determine the presence of each PICS-F impairment, four dichotomous dependent variables will be defined: psychological (PHQ-4  $\geq 6$  or IES-6  $\geq 1.75$ ), physical (SF-36 VT  $< 45$ ), and cognitive (MEFO  $< 9$ ) impairments at T3 and T4. Subjects scoring above or below the respective cut-off value will be categorized as having PICS-F in the respective impairment at T3 and/or T4.

**Statistical analyses:** To explore and characterize data, descriptive statistics will include the analysis of summary statistics and plots (e.g., histograms, q-q plots, and boxplots). Continuous normally distributed variables will be reported using means and standard deviations (SD) and non-normally distributed variables with medians and interquartile range (IQR). Categorical variables will be reported using frequency and percentages. For each questionnaire, internal consistency will be explored calculating Cronbach's alpha.

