Given that this study considers more than one measurement (repeated measures) over time, this information should be considered as correlated within-subjects. Therefore, to analyze variables associated with the PICS-F impairments over time, panel or longitudinal analysis will be used. First, graphical methods, such as panel line plots, will be used to visualize the trend and variation between and within-subjects over time. This analysis will be useful for determining some important covariates and the regression models to be included and applied afterward. Second, the strength of outcome correlation should be defined to decide the regression methods. In this scenario, and considering the nature of the outcome, generalized linear mixed models (GLMM) will be used. Contextual factors (family member and patient features) of each subject will be considered fixed effects, but random effects will be included because it is expected that the outcome in each time and for each subject will vary. Given that the outcome is measured as a dichotomous variable, the family will be binomial, and the link function is expected to be logit. Then, the model will be built starting with a large model and trimming it down according to statistical significance but also based on the proposed theoretical model (CSM). The initial models proposed for this study are presented in Table 1.

If family satisfaction (FS) or caregiver burden (CB) is associated with any of PICS-F impairments at T3 and/or T4, GLMM with and without the selected secondary stressor will be fitted to analyze the extent of this association. First, FS measured at T1 will be added to models 1-4 while the FS measure at T2 will be included in models 5-8. Similarly, CB measured at T3 will be included in models 9-20 while the T4 measure of CB will be added to models 17-20. The original model without a secondary stressor will be contrasted

with the same model plus the secondary stressor (either FS or CB). Scores such as Akaike Criterion and likelihood ratio tests will be performed and residual plots will be obtained. Also, 95% confidence intervals will be reported and a  $p$ -value  $< .05$  will be considered statistically significant. All statistical analyses will be conducted in R, using the applicable packages.

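### Every multivariable factor model uses a yes/no outcome cut from a score collected in full; full-score models should be added for aims 3 and 4

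*Protocol*

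**What the plan says.** Under METHODS, Variables, the protocol collects four scores. PHQ-4 is the sum of four items scored 0 to 3, so 0-12. IES-6 is a mean of items scored 0 to 4. SF-36 VT is averaged on 0-100. MEFO runs to 13 points.

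The Outcome paragraph then says: "To determine the presence of each PICS-F impairment, four dichotomous dependent variables will be defined". The cuts are PHQ-4 at 6 or more, IES-6 at 1.75 or more, SF-36 VT below 45 and MEFO below 9.

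The Statistical analyses paragraph on mixed models states: "Given that the outcome is measured as a dichotomous variable, the family will be binomial, and the link function is expected to be logit". That family covers the initial models in Table 1 (1 to 20). It also covers the comparison of each model with and without family satisfaction or caregiver burden, judged by the Akaike criterion and likelihood ratio tests.

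Specific aim 4 reads: "To evaluate the extent to which secondary stressors (family satisfaction or caregiver burden) significantly contribute to PICS-F impairments". Aim 3 and hypotheses 2 and 3 likewise concern association with, or contribution to, the impairments.

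The bivariate step is wider. It allows correlation, t-test or ANOVA, and rank tests where the dependent variable is continuous, and it helps to choose candidate predictors.

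**The concern.** The cuts are needed to count cases for the incidence aim. The protocol gives no reason why the multivariable factor models should see nothing else. On PHQ-4, a relative scoring 5 is then treated like one scoring 0, and one scoring 6 like one scoring 12.

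Aims 3 and 4 ask which factors matter and how much satisfaction or burden adds. If an association runs along the scale, models of the cut outcome can miss it when the collected data would have shown it. A null contrast for satisfaction or burden could then be taken as no contribution when it partly reflects the cut. The risk is greatest where cases are rare. Cognition may be such an outcome, since the Background considers marked impairment unlikely among relatives during the ICU stay.

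**Working it through.** **1. The plan's own figure.** Inputs from Sample Size: 95% confidence, precision 5%, and "a 20% incidence of PTSD symptoms reported in a study utilizing an IES-6" at the 1.75 cut.

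- Initial n = 1.96² × 0.20 × 0.80 / 0.05² = 245.9, so 246. The protocol says "the initial sample size is 247 RFM", a difference of one.
- Finite-population step with 600: 600 × 247 / (600 + 247) = 174.97, so 175.
- Losses of 40%: 175 / 0.60 = 291.7, so 292.

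The calculation reproduces. It sets the precision of one proportion. The stated 80% does not enter the formula, and no effect size is given for aims 3 and 4. I use n = 175, the number before inflation for losses.

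**2. Information kept by a cut.** For a normal score with a linear effect, the efficiency of a cut with prevalence p relative to the full score is φ(z_p)² / [p(1−p)]. At p = 0.20, z = 0.8416 and φ = 0.2800, so 0.0784 / 0.16 = 0.49.

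| Prevalence | Information kept |
|---|---|
| 5% | 0.22 |
| 10% | 0.34 |
| 20% (planning value) | 0.49 |
| 30% | 0.58 |
| 43% to 53% (fatigue, Background) | 0.63 to 0.64 |

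At 20%, 175 relatives carry the information of about 175 × 0.49 = 86.

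**3. Power for a normal score.** One predictor, two-sided 5%, 20% prevalence. Power = Φ(atanh(r) × √172 × √E − 1.96), with E = 1 for the full score and 0.49 for the cut. The correlation r is an assumption. Example, r = 0.20: 0.2027 × 13.11 = 2.66, giving 76%; 2.66 × 0.70 = 1.86, giving 46%.

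| r | Full score | Cut | Loss (points) |
|---|---|---|---|
| 0.10 | 26% | 15% | 11 |
| 0.15 | 51% | 28% | 22 to 23 |
| 0.20 | 76% | 46% | 30 |
| 0.25 | 92% | 65% | 27 |
| 0.30 | 98% | 81% | 17 |
| 0.35 | 99.8% | 92% | 8 |
| 0.40 | 100% | 97% | 3 |

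**4. Power for a coarse, floored score.** Simulation at n = 175: a latent normal outcome is mapped to a 13-level 0-12 score with the stated share of relatives at or above 6 and an assumed share at 0. A logit likelihood-ratio test on the cut is compared with linear regression on the score. Entries are cut against full score.

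| Cases, share at 0 | r = 0.15 | r = 0.20 | r = 0.25 |
|---|---|---|---|
| 20%, 20% | 29% vs 47% | 47% vs 74% | 66% vs 90% |
| 20%, 50% | 29% vs 40% | 47% vs 66% | 64% vs 83% |

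The differences are 18, 27 and 24 points, then 11, 19 and 19. A repeat run gave 18, 24 and 23, then 12, 18 and 18. The loss is therefore about 12 to 27 points. A Spearman test came within about 3 points of the linear result. With 45% of relatives as cases and 50% at the floor, the gain from the full score fell to 7 to 8 points.

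**5. Where the direction can reverse.** Suppose a predictor shifts only the odds of being a case and not the score within cases or non-cases (n = 175, 20% cases, 40% at zero, log-odds 0.5 per SD). Power was then 74% for the logit, 55% for linear regression and 44% for Spearman.

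**6. Practical setting.** At 20% of 175 there are 35 cases. Table 1 model 1 lists 5 patient variables, 8 family variables and 5 questionnaire scores, so 18 predictors before factor coding: 35 / 18 is about 2 cases per predictor.

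**Limits.** Steps 3 and 4 use one predictor and no random effects. The tests run on the full score were linear and Spearman; no cumulative-logit fit and no MEFO-shaped score was simulated.

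**The case against.** The strongest defence is that caseness is the construct. The Outcome paragraph defines impairment by the cut-offs, and the aims and hypotheses are worded in terms of impairments. A logit model answers that directly, while a full-score model estimates severity, including differences below the cut-off. This stands, and it is why the binary models should stay rather than be demoted.

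Three further points stand. The bivariate step does allow continuous dependent variables, so full-score associations are not shut out of aim 3 altogether. The study is labelled exploratory, is sized for an incidence, and promises no power for aims 3 and 4. Nothing in the protocol says that a null contrast would be reported as no contribution; that is a risk of interpretation.

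A reader might infer that the plan loses half the information on all four scales and a fixed amount of power. The documents do not support this. One half belongs to 20% prevalence and a roughly normal score, and the power figure needs an effect size that the protocol does not give. A reader might also take the phrase about measurement as a false description of the instruments. It more plausibly refers to the variables that the Outcome paragraph defines, so it is loose wording.

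None of this explains why no multivariable model uses the full scores. An unseen analysis plan might add such models, but the protocol itself fixes the binomial family for all of Table 1.

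**Conclusion.** The point holds for the multivariable models and the satisfaction and burden contrasts. For a roughly normal score and an effect along the whole scale, the cut keeps about 49% of the information at 20% prevalence, about 63% near the fatigue rates cited, and 22-34% at 5-10%.

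The cost in power is conditional. For a coarse, floored 0-12 score with n = 175, 20% prevalence and assumed r of 0.15 to 0.25, it is about 12 to 27 points. It shrinks for stronger effects, or for a heavy floor with high prevalence, and could change sign if a factor acts only at the cut-off. This is an inexpensive improvement using data already collected. It does not make the planned caseness models invalid.

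**What to change.** In the Statistical analyses section:

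- Keep the cut-offs for incidence, and keep the binary mixed models for the defined impairments.
- Add prespecified models of the full T3 and T4 scores for aims 3 and 4, including the contrasts with and without satisfaction or burden: cumulative-logit models for PHQ-4, IES-6 and MEFO, and a linear or ordinal model for SF-36 VT. Include random effects wherever repeated measures are modelled together.
- Report severity and caseness results side by side, so that a null binary contrast is not read alone as no contribution.
- Reword the sentence on the outcome to say that the scores are dichotomised to define caseness.

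Before SF-36 VT is modelled in full, its direction must be reconciled: Variables says higher means more fatigue, yet the cut-off classes low scores as fatigued.

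The cost is protocol wording and a second set of models in R, with no new data or participants. There will be a severity estimand to report beside caseness, and proportional-odds or residual assumptions to check.

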### Theoretical Framework

To provide a conceptual organization of the current and potential variables that may be influencing PICS-F impairments, this study will employ an adapted version of the *Pearlin's Caregiver Stress Model* (CSM). In brief, the CSM aims to explain the occurrence of negative outcomes among caregivers (e.g., depression, anxiety, cognitive disturbances, etc.) based on the interaction of the background and contextual factors (family member and patient-related), primary stressors (objective and subjective indicators), and secondary strains (role and intrapsychic). Besides, the relationships between the CSM elements are mediated by psychosocial resources (coping or social support).

In this study, the negative outcomes will be PICS-F impairments (psychological, physical, or cognitive) that are influenced by contextual factors and primary stressors (psychological, physical, and cognitive) experienced by family members during ICU admission/stay and after hospital discharge. Then, secondary stressors can contribute to PICS-F impairments either during the ICU stay (family satisfaction) or after hospital discharge (caregiver burden). In both scenarios, psychosocial resources (social support and resilience) may buffer the primary stressors, secondary stressors, and outcomes. Figure 1 presents the proposed modified version of the CSM model for PICS-F impairments for this study.

[figure not shown]

**Figure 1.** Caregiving Stress Model adapted to Post Intensive Care Syndrome – Family impairments.

**Research questions:** The research questions that will guide the study are: In a sample of family members of ICU survivors of a public hospital in Chile:

- 1) what is the incidence rate of each PICS-F impairment at three and six months after hospital discharge?
- 2) what are the contextual factors, primary stressors, secondary stress, and psychosocial resources associated with each PICS-F impairment at three and six months after hospital discharge?
- 3) If family satisfaction or caregiver burden is associated with PICS-F impairments, to what extent do they contribute to these outcomes at three and six months after hospital discharge?

**Objective:** The aim of this study is two-fold, one cross-sectional and one longitudinal aim.

(1) To determine the incidence of each PICS-F impairment (psychological, physical, and cognitive) among family members of ICU survivors of a public hospital in Chile.

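### Family satisfaction and caregiver burden get their adjusted analysis only after an undefined association in the same data, although aim 4 and hypothesis 3 set no such condition

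*Protocol*

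**What the plan says.** The paragraph on secondary stressors in the protocol's Statistical analyses opens with a condition: "If family satisfaction (FS) or caregiver burden (CB) is associated with any of PICS-F impairments at" three and/or six months after discharge. Once it is met, "GLMM with and without the selected secondary stressor will be fitted". The two fits are compared by Akaike criterion and likelihood ratio test, with 95% confidence intervals and p < .05.

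The same paragraph assigns each stressor to blocks of models. Satisfaction at T1 goes to models 1-4 and satisfaction at T2 to models 5-8. Burden at T3 "will be included in models 9-20 while the" T4 measure goes to models 17-20. Table 1, which lists the predictors of all 20 models, has no column for either stressor.

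The objectives do not agree on the condition. Research question 3 has it: "If family satisfaction or caregiver burden is associated with PICS-F impairments, to what extent do they contribute to these outcomes". Specific aim 4 does not: "To evaluate the extent to which secondary stressors (family satisfaction or caregiver burden) significantly contribute to PICS-F impairments among family members". Hypothesis 3 does not either. It predicts that at least one of the two stressors contributes to at least one impairment after adjustment for the other groups of factors.

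**The concern.** Hypothesis 3 names two variables in advance and makes an adjusted claim about them. The plan tests that claim only if a preliminary association appears in the same sample, and two things follow.

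- **A stressor that fails the screen is left out.** It enters no model, so the protocol yields no adjusted estimate for it. That includes any effect that shows only after adjustment. Aim 4 and hypothesis 3 then go unanswered for that stressor.
- **A stressor that passes is estimated conditionally.** The quantity wanted is the extent of its contribution. An estimate produced only after a significance screen on the same data tends away from zero, and the ordinary interval does not allow for this.

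The screen is also undefined. The preceding paragraphs describe bivariate tests that, together with the literature, help to choose variables. Since no model in Table 1 contains satisfaction or burden, those bivariate tests are the natural source of the association, but the text does not say so. Nor does it give a threshold.

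**Working it through.** **Inputs from the protocol.** Expected incidence 20%, alpha 5%, precision 5 points, finite population 600, losses 40% (Sample Size). Four dichotomous variables at T3 and T4 (Outcome), which gives 4 × 2 = 8 outcome-by-time combinations. Models 1-8 are run separately for T3 and T4 (footnote to Table 1).

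**Assumptions, not in the protocol.** The stressor's log odds ratio per SD (0.10 to 0.50, plus zero), equal for all eight outcomes. Its correlation with another predictor (0 or 0.3). A screen by unadjusted logistic regression at p < .05.

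**Step 1: the planned sample size.** 1.96² × 0.20 × 0.80 / 0.05² = 245.9 (stated 247). 600 × 247 / 847 = 174.97, so 175. 175 / 0.6 = 291.7, so 292. The figures reproduce apart from a trivial difference at the first step. The analysis set is 175.

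**Step 2: the listed contrasts.** Satisfaction: 8 models × 2 times = 16. Burden: 12 models for the T3 measure + 4 for the T4 measure = 16. In total 32, of which 32 × 0.05 = 1.6 would fall below .05 by chance if all were null.

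**Step 3: how often a null stressor passes.** With independent tests, 1 − 0.95⁸ = 0.34. With 16 tests (satisfaction is measured twice), 1 − 0.95¹⁶ = 0.56.

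**Step 4: simulation of the two readings.** n = 175, eight correlated outcomes of roughly 20% prevalence, an unadjusted screen, then a logistic model adjusted for five covariates; 1,500 replicates per setting. Entries are mean adjusted log odds ratios, for correlation 0 / 0.3.

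| True value | No screen | One association releases all models | Screen per outcome |
|---|---|---|---|
| 0.20 | 0.198 / 0.200 | 0.227 / 0.210 | 0.519 / 0.431 |
| 0.30 | 0.297 / 0.303 | 0.312 / 0.305 | 0.549 / 0.466 |
| 0.50 | 0.507 / 0.505 | 0.507 / 0.505 | 0.624 / 0.571 |

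For a true 0.20 (odds ratio 1.22), the third column corresponds to odds ratios of 1.25 / 1.23 and the fourth to 1.68 / 1.54.

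**Step 5: a closed-form check of the per-outcome reading.** SE = 1/√(175 × 0.16) = 0.189. Screening and estimating on the same unadjusted coefficient at |z| > 1.96, a true odds ratio of 1.3 passes 28% of the time and then averages 1.63 (log odds ratio 1.9 times too large). A true 1.5 passes 57% and averages 1.71 (1.3 times).

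**Step 6: how often a stressor is left out.** In the simulation, the share of samples with no association at all, so that the stressor enters no model:

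| True value | Correlation 0 | Correlation 0.3 |
|---|---|---|
| 0.10 | 1 − 0.429 = 57% | 1 − 0.757 = 24% |
| 0.20 | 1 − 0.687 = 31% | 1 − 0.931 = 7% |
| 0.30 | 1 − 0.885 = 12% | 1 − 0.989 = 1% |

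Confounding that hides an effect until adjustment was not simulated.

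**The case against.** The strongest objection concerns size. The text opens the gate on an association with any impairment and then adds the stressor to whole blocks of models. Read literally, one association releases all contrasts for that stressor, null ones included. A reader might infer that the reported odds ratios will be badly overstated, for example 1.3 reported as 1.63. That figure needs a separate screen for each outcome, which the protocol does not describe. It also screens and estimates on one unadjusted coefficient, whereas the plan reports adjusted ones. This objection stands.

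A reader might also infer that null contrasts will be withheld. The protocol nowhere says so, and it states that confidence intervals will be reported. A stressor that fails the screen still appears in the bivariate analyses and under specific aim 3. What it lacks is the adjusted estimate.

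Nor does the screen raise the overall type I error. For a null stressor under the literal reading, 13% (correlation 0) or 8% (correlation 0.3) of the contrasts that get fitted are significant. Multiplied by the chance of being fitted, that is 0.329 × 0.13 = 4.3% and 0.503 × 0.08 = 4.0% of all contrasts.

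It is fair to add that research question 3 is itself conditional, so the analysis follows one of the protocol's own statements, and that the title calls the study exploratory. This softens the criticism but does not remove the conflict with aim 4 and hypothesis 3.

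Finally, removing the screen will not by itself give unbiased odds ratios. Model 1 lists 18 predictors (5 patient, 8 family member, 5 questionnaires) against about 175 × 0.20 = 35 events. In a simulation without any screen, with 18 independent covariates (five with an assumed log odds ratio of 0.3; 3,000 replicates), a true 0.20 averaged 0.245 and a true 0.30 averaged 0.359, about 20% too large. That exceeds the effect of the screen under its literal wording.

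**Conclusion.** The point holds in a limited form. The protocol makes the adjusted analysis of satisfaction and burden depend on an undefined association in the same cohort, while aim 4 and hypothesis 3 ask for it without condition. The firm consequence is that a stressor failing the screen gets no adjusted estimate. That follows from the text and Table 1 and needs no assumption about effect size.

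The second consequence, inflation for a stressor that passes, is sure in direction but depends on the reading. Under the literal wording it is about 5% to 14% for a true log odds ratio of 0.20 (0.210 and 0.227 against 0.20), at most about 4% for 0.30, and nil for 0.50. Applied per outcome, it would be 2.2 to 2.6 times for 0.20. These sizes rest on the assumed effects, correlations and p < .05 screen. The sample size is unaffected. This is a cheap improvement to an exploratory cohort study, not a flaw that endangers it.

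**What to change.** In Statistical analyses, delete the condition at the start of the secondary-stressor paragraph. State instead that, for satisfaction and burden, each model to which the paragraph already assigns them will be fitted with and without the stressor whatever the bivariate results. State also that the odds ratio, 95% confidence interval and likelihood ratio test will be reported for every such pair. Remove the conditional clause from research question 3 so that it agrees with aim 4 and hypothesis 3. Fit both members of a pair on the same relatives, because burden is not collected from those with no caregiving tasks.

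If the investigators prefer to keep a screen, the protocol should name the test and threshold, say whether it applies per outcome or once per stressor, and label the resulting estimates as exploratory.

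The cost is a few extra model fits, up to the 32 contrasts already listed, with no added participants or data. The set of contrasts is then fixed in advance. The number of predictors per event remains a separate problem.
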